## Abstract

**Introduction:**

The judiciary sector faces high absenteeism due to mental health issues, yet applying effective therapies like mindfulness and trial-based cognitive therapy (TBCT) remains unexplored.

**Objectives:**

Develop and apply Mindfulness-Integrated Trial-Based Cognitive Therapy (M-TBCT) in the judiciary to assess its acceptability, feasibility, and efficacy in enhancing psychological well-being and reducing depression, anxiety, and improving self-care.

**Methods:**

Conduct a controlled, randomized study in two phases: Phase 1 involves a pilot study to structure the M-TBCT protocol and test its acceptability and feasibility in the judiciary (*N* = 30); Phase 2, an efficacy trial with 90 participants, comparing M-TBCT to a waitlist. M-TBCT consists of 8 online, individual, weekly sessions. Participants recruited via SRQ-20, with WHO-5, PHQ-9, GAD-7, CD-QUEST and ASAS-R as outcomes.

**Expected outcomes:**

M-TBCT is expected to be acceptable, feasible, and effective in improving psychological well-being, reducing anxiety, depression, and enhancing self-care, with sustained benefits at a 6-month follow-up.

**Conclusions:**

This study introduces a novel psychotherapeutic approach to address mental well-being and self-care in the judiciary.

Specifications table

**Table utbl0001:** 

Subject area:	Psychology
More specific subject area:	Mindfulness and trial-based cognitive therapy
Name of your protocol:	Mindfulness-Integrated Trial-Based Cognitive Therapy
Reagents/tools:	N.A.
Experimental design:	This is a mixed methods study (quantitative-qualitative) divided into two phases: a pilot study to structure the M-TBCT protocol and test its acceptability and feasibility (phase 1) and efficacy trial of M-TBCT, single-blind, with two parallel arms (phase 2).
Trial registration:	Ensaiosclinicos.gov.br: U1111–1304–1781.
Ethics:	This study was approved by the Research Ethics Committee of the Federal University of São Paulo (CAAE 73,817,423.3.0000.5505). Participants will sign the Informed Consent Form online and data confidentiality will be guaranteed.
Value of the Protocol:	1) First randomized and controlled feasibility study that structures a protocol integrating psychotherapeutic tools validated in the literature and three assessment points (baseline, post-intervention and 6-month follow-up) 2) This randomized, controlled study aims to fill a gap in scientific evidence-based interventions to promote well-being in the judiciary 3) Improvements in well-being and self-care are expected, as well as a reduction in levels of anxiety, depression and cognitive distortions.

## Background

Recent psychological research has increasingly emphasized the importance of promoting well-being and positive mental health, aligning with the World Health Organization's definition of health as “a state of complete physical, mental, and social well-being” [1]. Carol Ryff's multidimensional model of psychological well-being, encompassing aspects such as self-acceptance, autonomy, environmental mastery, purpose in life, positive relations with others, and personal growth [2], serves as a foundation for our study.

Mindfulness and cognitive therapy have demonstrated positive effects on mental health in various workplace settings [3,4]. Jon Kabat-Zinn's mindfulness approach, centered on present-moment awareness and non-judgment [5], has been adapted for diverse contexts, including the Mindfulness-Based Health Promotion Protocol (MBHP; [6]). This protocol has shown efficacy in improving mental health across multiple randomized controlled trials [[7], [8], [9]], addressing issues such as chronic pain [10], burnout [11], and obesity [12].

Trial-Based Cognitive Therapy (TBCT), an innovative extension of Cognitive-Behavioral Therapy (CBT) developed by [name] [13], focuses on challenging dysfunctional thoughts, emotions, and behaviors. TBCT's unique courtroom metaphor approach has proven effective in treating a range of mental health conditions, including depression, suicidal ideation [14,15], social anxiety [16], PTSD [17], and OCD [18]. This approach combines traditional CBT techniques with elements from other psychotherapies [19,20].

The judiciary sector, vital for societal function, has witnessed a concerning rise in mental health problems, intensified by the Covid-19 pandemic [21]. Symptoms such as fatigue, mood changes, and sleep disturbances have been reported among judicial staff [22].

In response to these challenges, our study aims to develop and implement Mindfulness-Integrated Trial-Based Cognitive Therapy (M-TBCT) specifically tailored for the judiciary context. Through a pilot phase and a subsequent randomized controlled trial, we will evaluate the acceptability, feasibility, and efficacy of M-TBCT in enhancing psychological well-being, reducing depression and anxiety symptoms, and promoting self-care practices among judiciary professionals.

This research seeks to contribute to the development of targeted interventions that foster a healthier and more resilient judiciary workforce, potentially informing future occupational health initiatives. The primary objectives are to refine the M-TBCT protocol, assess its acceptability and feasibility within the judiciary, and compare its efficacy against a waitlist control group, measuring its impact on key mental health outcomes such as depression, anxiety, cognitive distortions and self-care.

## Description of protocol

### Study design

This study consists of two phases. The first is a pilot study to develop the M-TBCT protocol, assessing its suitability and practicality within the judicial context. The second phase is an efficacy trial using a single-blind design with two groups: an M-TBCT intervention group and a waitlist control group. Inspired by Soler et al. [23], the first phase will involve a sample of 30 participants, divided into three blocks of 10, each receiving M-TBCT in eight weekly one-hour sessions. Participant feedback via a self-report questionnaire will guide protocol refinement.

The second phase, an efficacy trial, will have 90 participants randomly assigned to either the intervention or waitlist group, each receiving the same M-TBCT regimen. The M-TBCT protocol will be administered individually on a weekly basis, with each session lasting 1 h and totaling 8 online sessions.

### Evaluation measures

Assessments will occur pre-intervention (T0), post-intervention (T1), and at a six-month follow-up. These will include questionnaires measuring well-being (WHO-5), depression (PHQ-9), anxiety (GAD-7), reduction in cognitive distortions (CD-QUEST) and self-care (ASAS-R). Post-study, M-TBCT will be offered to the waitlist group if results are favorable. The study stages will follow the CONSORT flowchart [24] depicted in Fig. 1. The study was approved by the Research Ethics Committee of the Federal University of São Paulo (CAAE 73817423.3.0000.5505) and registered in the Brazilian Clinical Trials Registry (REBEC) 〈https://ensaiosclinicos.gov.br/〉.

**Fig. 1 fig0001:**
[figure not shown]
Study flowchart (CONSORT). M-TBCT: Mindfulness-integrated trial-based cognitive therapy.

### Hypotheses

Based on prior research, we hypothesize:

Hypothesis 1 (H1)M-TBCT will demonstrate acceptance and feasibility among judges and public servants in the judiciary.

Hypothesis 2 (H2)M-TBCT will significantly improve psychological well-being, self-care, and reduce anxiety, depression and cognitive distortions compared to the control group.

Hypothesis 3 (H3)The benefits of M-TBCT will be maintained at the six-month follow-up.

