### Sample size (Phases 1 and 2)

The sample will consist of magistrates and public servants from the judiciary who score a minimum of 7 points on the recruitment instrument (SRQ-20), which is available for online completion throughout the regional jurisdiction via an electronic platform integrated into TRT5’s intranet.

The sample size for Phase 1 of the study was determined with Soler et al. [23] as a reference, considering a minimum of 30 participants. For Phase 2, the study primarily referred to a meta-analysis conducted by Khoury et al. [39], which assessed the effectiveness of 8-week mindfulness-based interventions in healthy individuals and found an average dropout rate of 10 %.

To establish statistical significance, a sample size of 72 individuals was estimated using G*Power 3.1.9.2, based on a one-tailed *t*-test for independent samples with α=0.05, β=0.20, and Cohen's *d* = 0.6. Considering an approximate dropout rate of 25 %, which is higher than that found in similar studies, an estimated recruitment of approximately 90 eligible individuals for the intervention and control groups is anticipated.

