Randomization success will be determined by no significant differences between the groups regarding demographic and clinical characteristics. Continuous variables will be analyzed using Student's *t*-test, and categorical variables will be analyzed using chi-square or Fisher's exact tests. Longitudinal data (T0, T1, and T2) for both intervention and passive control (waitlist) groups will be tracked using the repeated measures Student's *t*-test. Spearman's correlation test will assess variable correlations. M-TBCT program efficacy will be evaluated using repeated measures ANOVA to examine the main effects of time and treatment and their interaction. McNemar's test will assess changes in mental disorder risk classification after M-TBCT intervention. Effect sizes (Cohen's d) and 95 % CI will be calculated for intra- and inter-group comparisons (intervention and waitlist). The Bonferroni correction will be applied to adjust for various statistical tests.

The data will be analyzed through intention-to-treat (ITT), including all randomized participants in their initially assigned group, regardless of completing the treatment protocol. Per-protocol analysis will exclude participants with fewer than four sessions (50 % of the M-TBCT program). Attrition analysis (As-treated) will compare those who completed the protocol with those who responded only to the initial questionnaire. This study employs mixed-effects linear models (MLMs) for statistical analysis. Fixed variables, including depression, anxiety, and self-care, will be incorporated, whereas random variables will be introduced to capture intra-individual variation over time. This will enable modeling of unexplained individual differences not accounted for by the fixed variables, providing a robust approach to understanding the relationships between these variables and well-being throughout the study.

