Mediation analysis will be employed to examine the potential interaction among variables, notably depression (PHQ-9), anxiety (GAD-7), cognitive distortions (CD-QUEST) and self-care (ASAS-R), and the primary outcome, represented by well-being (WHO-5). These independent variables will be assessed for their direct impact on well-being, while sociodemographic variables such as gender, age, socioeducational level, income, marital status, number of children, occupation, and working hours will be treated as covariates in the mediation analysis to control for potential confounding factors. All statistical analyses will be conducted using SPSS 28.0 software, with a significance level of 5 % for all study hypotheses.

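### H3 (benefit maintained at six months) has no assigned contrast, and neither the within-arm paired t-tests nor the omnibus time-by-treatment interaction can establish it

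*Protocol article*

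**What the plan says.** The Hypotheses section lists three hypotheses. The third is "The benefits of M-TBCT will be maintained at the six-month follow-up". It gives no margin, no retained fraction and no named comparison.

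For Phase 2, the Statistical methods section names these analyses:

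- **Within-arm tests:** "Longitudinal data (T0, T1, and T2) for both intervention and passive control (waitlist) groups will be tracked using the repeated measures" Student's t-test.
- **Efficacy:** "repeated measures ANOVA to examine the main effects of time and treatment and their interaction".
- **Effect sizes:** Cohen's d with 95% CI "will be calculated for intra- and inter-group comparisons (intervention and waitlist".
- **Mixed models:** "Fixed variables, including depression, anxiety, and self-care, will be incorporated". The listed fixed terms are other outcome scales; arm, visit and arm-by-visit are not among them.
- **Multiplicity and level:** "The Bonferroni correction will be applied to adjust for various statistical tests", "with a significance level of 5 % for all study hypotheses".

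None of these is linked to H3. The Results section and Table 2 have every scale completed by both arms at baseline, after the eight sessions and at six months. Evaluation measures says the waitlist may be offered M-TBCT only once the study is over. A randomised comparison at six months (T2) is therefore available.

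**The concern.** Maintenance claims two things: that a treatment benefit exists after the intervention, and that it has not been materially lost by six months. Both concern the difference between the arms. The named tests do not address that pair of statements.

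- **Paired T0-T2 test in the M-TBCT arm.** It mixes treatment effect with spontaneous recovery and regression to the mean. Participants enter because they score 7 or more on the SRQ-20, so some improvement without treatment is plausible.
- **Paired T1-T2 test in the M-TBCT arm.** A significant fall would argue against maintenance, but a non-significant result establishes nothing. The lower the power, the more often loss goes unseen.
- **Omnibus interaction.** It asks whether the arm difference varies in any way over three visits. Rise and hold, and rise and full relapse, both satisfy it.

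H3 is a named hypothesis, and sustained benefit is repeated in the abstract and the conclusions. At stake is a maintenance claim resting on tests that do not bear on it, when the data for a better answer are being collected anyway.

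**Working it through.** **Inputs from the article.** Sample size section: "α=0.05, β=0.20, and Cohen's *d* = 0.6", one-tailed independent t-test, 72 evaluable, so 36 per arm at 1:1. Significance level 5%.

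**Assumptions.** The correlation r between visits is not given, so a range is shown. Compound symmetry with a common SD is assumed. All effects are in SD units. Loss of half the design effect, 0.6 / 2 = 0.3 SD, is illustrative, because the article sets no margin.

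**1. The plan's own figure.** Exact noncentral-t, one-sided 5%, d = 0.6: 36 per arm gives power 0.809, so 72 in total is reproduced.

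**2. Omnibus interaction.** Let the arm difference at T0, T1, T2 be δ. Then λ = (n/2) · Σ(δ − mean δ)² / (1 − r), with 2 and 2(2n − 2) = 140 degrees of freedom.

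- Fully kept, δ = (0, 0.6, 0.6): mean 0.4, sum of squares 0.16 + 0.04 + 0.04 = 0.24.
- Fully lost, δ = (0, 0.6, 0): mean 0.2, sum of squares 0.04 + 0.16 + 0.04 = 0.24.
- Half lost, δ = (0, 0.6, 0.3): mean 0.3, sum of squares 0.09 + 0.09 + 0 = 0.18.

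The first two are identical, so λ = 18 × 0.24 / (1 − r) in both.

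| r | λ, kept or lost | Power, fully kept | Power, fully lost | Power, half lost |
|---|---|---|---|---|
| 0.5 | 8.64 | 0.74 | 0.74 | 0.61 |
| 0.6 | 10.80 | 0.84 | 0.84 | 0.71 |
| 0.7 | 14.40 | 0.93 | 0.93 | 0.84 |

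A significant interaction therefore cannot separate maintenance from complete loss.

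**3. Paired T1-T2 test if half the effect is lost.** dz = 0.3 / √(2(1 − r)), noncentrality dz·√n, two-sided. At r = 0.5, dz = 0.3 / 1 = 0.30 and the noncentrality with n = 36 is 1.80. Probability of a non-significant result:

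| r | n = 36, 5% | n = 45, 5% | n = 36, Bonferroni over 3 visit pairs |
|---|---|---|---|
| 0.5 | 58% | 50% | 75% |
| 0.6 | 50% | 40% | 68% |
| 0.7 | 38% | 28% | 57% |
| 0.8 | 21% | 12% | 37% |
| 0.9 | 3% | 1% | 7% |

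n = 45 is one full arm of the planned 90. The article does not define the Bonferroni family; three visit pairs is one possible choice. A stricter threshold makes a real loss harder to see.

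**4. What the randomised comparison offers.** A plain between-arm test at T2 with 36 per arm and d = 0.6 fully kept has power 0.81 one-sided or 0.71 two-sided. With half kept (d = 0.3) it is 0.35 or 0.24. For the T1-to-T2 change in the arm difference, SE = √(2(1 − r)) · √(2/36). With t = 1.994 on 70 df, the 95% CI half-width is 0.47, 0.42, 0.36, 0.30 and 0.21 SD at r = 0.5, 0.6, 0.7, 0.8 and 0.9.

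**The case against.** A reader might infer that H3 is left to the within-arm paired t-tests alone. The article does not support that. It also plans the interaction ANOVA, between-arm effect sizes with 95% CI and mixed models, and it runs the paired tests in both arms, so the waitlist would display natural recovery. A between-arm effect size computed at T2 would supply part of the answer.

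A reader might also infer that a non-significant T1-T2 change would be declared maintenance. No such rule is stated. The miss rates in step 3 are thus conditional on a decision rule, a loss and a correlation that the article does not give; at r = 0.9 they nearly vanish.

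A further objection is scope: this is a condensed article, and matching contrasts to hypotheses is often left to an analysis plan. That would answer a complaint about mere silence. The article, however, names its tests, and those tied to the three visits do not fit the hypothesis; the between-arm effect sizes are not assigned to a visit or to H3.

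Finally, a T2 difference shows that a benefit is present at six months, not that all of it was kept. That objection stands, and the fix has to say so.

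**Conclusion.** The point holds in this form: H3 has no assigned contrast, and neither the paired t-tests nor the omnibus interaction can establish it. The equality of the interaction's power under full maintenance and full loss follows from the symmetry of the two profiles, so under compound symmetry it holds at every r; the values 0.74 to 0.93 assume 36 per arm and r = 0.5 to 0.7. The miss rates of 58% down to 3% illustrate what would follow if non-significance were taken as maintenance, which the article neither states nor rules out. They rest on a 0.3 SD loss, 36 completers, r from 0.5 to 0.9 and no multiplicity correction. The point does not touch the efficacy comparison at T1.

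**What to change.** - Assign H3 to the baseline-adjusted between-arm difference in WHO-5 at T2, in all randomised participants, from a mixed model with arm, visit and arm-by-visit terms.
- State that this contrast shows a benefit present at six months.
- Report the T1-to-T2 change in the between-arm difference with its 95% CI, as the estimate of how much benefit is retained.
- Label the within-arm paired t-tests descriptive, and state that maintenance will not be inferred from a non-significant change or from the omnibus interaction.

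**Cost.** Analysis wording only; no new data or visits. The retention interval will be wide at 36 per arm (about ±0.36 to ±0.47 SD for r = 0.7 down to 0.5), so the conclusion on maintenance becomes more cautious. A formal retention test is not a realistic alternative: with an illustrative margin of 0.3 SD, no true loss and one-sided 2.5%, the randomised version has power 0.25, 0.30, 0.38 and 0.52 at r = 0.5, 0.6, 0.7 and 0.8. Estimation is the proportionate remedy.

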### Participants

After the study protocol is publicized through institutional media such as videos, website, and emails, interested individuals will be selected using the SRQ-20. Those scoring 7 points or higher and meeting other eligibility criteria will be invited via email by the researcher as part of a care initiative aimed at learning and practicing evidence-based skills to develop autonomy and self-efficacy in promoting psychological well-being. During this invitation, participants will receive explanations about how the study will work, and those who agree to participate will sign the informed consent form. After completing the self-assessment questionnaires, the first thirty participants will proceed to phase 1 of the study. Upon completion of phase 1, other ninety participants scoring 7 or higher on the SRQ-20 and meeting other eligibility criteria will proceed to phase 2 of the study, being randomized into one of the two arms (M-TBCT or waitlist for treatment).

### Inclusion criteria

Individuals eligible to participate in this study (phases 1 and 2) are adults of both sexes, employees, or judges of TRT5, aged 18 years or older, with a score of 7 or more on the SRQ-20. Participants should be able to read, write, and follow instructions and must have internet access.

### Exclusion criteria

Candidates meeting any of the following criteria will be excluded from participating in this study: self-declaration of severe symptoms of any mental disorder or ongoing organic disease; having a personality disorder, a diagnosis of schizophrenia, psychotic disorder, suicidal ideation, or drug use causing cognitive impairments in attention and concentration; being in the early stages or adjusting to pharmacological and/or psychotherapeutic treatment; and being a regular practitioner of mindfulness, meditation, or similar practices.

### Study settings

Eligible participants may be located in Salvador or any other city within the state covered by TRT5. TRT5, located in Salvador, will be the study headquarters and the headquarters of one of the lead researchers. The Federal University of São Paulo, the academic institution responsible for the study, is also the headquarters of one of the lead researchers and the Federal University of Bahia, the academic institution of another lead researcher.

### Intervention

The presented M-TBCT protocol will be applied individually and online through the Google Meet platform. Sessions will be held weekly, each lasting 1 h, totaling eight sessions over 2 months.

As mentioned, M-TBCT is an integration of two protocols, Mindfulness-Based Health Promotion (MBHP) and Trial-Based Cognitive Therapy (TBCT), which have shown promising results across various populations:

**Mindfulness-Based Health Promotion Protocol (MBHP):** Developed by [name] and inspired by Jon Kabat-Zinn's Mindfulness-Based Stress Reduction (MBSR), MBHP embodies the core principles of mindfulness, focusing on present-moment awareness with acceptance and non-judgment [6].

The MBHP aims to cultivate and enhance the state of consciousness regarding internal and external phenomena, thus fostering awareness. The program contributes to improved decision-making, conscious choices, defusion, enhanced socioemotional skills, and well-being. It is designed for application in both clinical (ill) and non-clinical (healthy) populations [6].

The MBHP is a structured program with a limited number of sessions that targets individuals aged 18 years and above. It is recommended for those without severe symptoms, not diagnosed with mental or organic disorders, not undergoing treatment adjustments, and those without personality disorders. The program can be implemented in group or individual settings. The latter format, as explored in this study, involves approximately 8 weekly sessions, each lasting 1 h [6].

This approach is significant because of its adaptability to different cultural contexts and has demonstrated efficacy in diverse populations. For instance, MBHP has been effective in reducing burnout in police officers [11], enhancing the quality of life in older adults [25], and serving as a complementary intervention in obesity treatment [12]. These findings suggest that the versatile nature of MBHP could be beneficial in addressing the unique stressors faced by judiciary professionals.

**Trial-Based Cognitive Therapy (TBCT):** TBCT, developed by Brazilian psychiatrist [name], is grounded in cognitive-behavioral therapy and uses experiential techniques to modify dysfunctional thoughts, emotions and behaviors.

The main TBCT techniques employ an analogy to the judicial process, guiding the patient toward decentering through metacognition and enabling a new perspective on negative core beliefs. The TBCT model operates in contrast to the automatic and uncritical mode of functioning that individuals often adopt when negative core beliefs are activated, justifying, in the latter case, the production and maintenance of symptoms. Previous studies have demonstrated the efficacy of TBCT in reducing psychological symptoms compared to traditional CBT [16].

It has been notably effective in treating various psychological disorders such as major depression [15], social anxiety [16,26], PTSD [17], suicidal ideation in major depressive disorder [14], obsessive-compulsive disorder and other adverse conditions [26,27]. This broad range of applicability underscores TBCT's potential effectiveness in the judiciary context, where mental health issues like stress, anxiety, and depression are prevalent.

The M-TBCT protocol (Table 1) integrates mindfulness, compassion, and TBCT strategies to develop metacognitive and socio-emotional skills that enhance well-being, self-care, and health-related quality of life. In simpler and accessible language, participants will be informed that the intervention focuses on learning and practicing evidence-based skills to promote psychological well-being. Mindfulness and self-compassion strategies are derived from the Mindfulness-Based Health Promotion (MBHP) protocol.

**Table 1 tbl0001:** Structure of the mindfulness protocol integrated with trial-based cognitive therapy (M-TBCT).

Sessão*	Interventions/Techniques	Homework assignments
**1. Getting off autopilot**	Cognitive conceptualization diagram (level I) CD-Quest-9 Raisin practice	CD-Quest-9 Text “What *mindfulness* is and isn't” Informal: *Mindfulness* (a part of the meal).
**2. Mindfulness and cognitive distortions**	Practice “Body Scan” Complete Intrapersonal Thought Record (with or without action plan)	Action plan (if built in the session) Text “Why practice *mindfulness*?” Formal: Body Scan
**3. The body and its relationship with thoughts, emotions and behaviors**	Interpersonal Thought Record (RP-Inter) (with or without an action plan) or Participation Grid (for guilt/shame) Practice “Mindful breathing”	Action plan (if created in the session) Text “What to do with the body?” Formal: Mindfulness of breathing.
**4. Facing my fears**	Practice “3 steps” Cognitive conceptualization diagram (level II) Color-coded Symptoms Hierarchy (CCSH)	Action plan created in the session (CCSH) Informal: “3 steps” practice
**5. Expanding mindfulness**	Practice of basic “Sounds and Thoughts” Consensual role-play (CRP) for feared or desired + action plan	Action plan practiced in the session (RPC) Formal: “Sounds and Thoughts” Practice (basic)
**6. Changing Core Beliefs**	Advanced “Sounds and Thoughts” Practice (with tagging and metaphors) TBCT conceptualization diagram (level III) Trial I	Daily positive belief worked on in the session. Formal: “Sounds and Thoughts” Practice (advanced) Informal: bring full attention to walking or other daily physical activity.
**7. Developing positive beliefs**	Trial I (complete or new) Practice “Compassion” (for yourself and for others)	Diary positive belief worked on in the session. Text “Mindfulness and compassion”. Formal: Practice of “Compassion” Informal: choose
**8. Being my own therapist**	Trial II + Compassionate Letter Practice “Self-Compassion” Final feedback	Text “Practice mindfulness without practicing mindfulness. Acceptance of reality.” Curriculum based on the tools learned.

⁎ All sessions will have take-home proposals.

The structure of the M-TBCT protocol envisions a progressive cadence of strategies designed to stimulate autonomy, involving the self-application of learned tools. The intention is to start with the simplest and gradually develop a more gentle and open stance that supports individuals in restructuring dysfunctional cognitions through specific TBCT techniques. The three pillars of the intervention – mindfulness, self-compassion, and TBCT – will operate in an integrated manner from the beginning of the protocol application.

Another highlighted aspect is the introduction of brief and concise homework tasks, favoring the continued exercise of learned tools without generating overload that could discourage the therapeutic process. An alternative strategy is to encourage the construction of a personalized toolkit with the patient, allowing them to have at their disposal the practices that have proven most useful and aligned with their goals, choosing those most suitable for their daily life. Another innovation in this protocol is the possibility for individuals to record, at the end of each session, the practices perceived as most useful and easy to apply in their daily lives.

